#### Development of the C-short checklist and explanation of items

For the development of C-short we chose the 10 most important and poorly reported CONSORT items as identified by a group of CONSORT experts in a previous study conducted by Hopewell and colleagues.^30^ The selection of the items was based on expert opinion and empirical evidence whenever available.^30^ In addition, to enable peer reviewers to better understand the items, we added a short explanation for each of the 10 items. These short explanations were extracted and amended from the CONSORT explanation and elaboration paper^11^ and from COBWEB which is an online writing aid tool.^33^ The short explanation was discussed and adapted by the scientific committee.

### Outcomes

#### Primary outcome

The primary outcome of this study will be the difference in the mean proportion of adequately reported C-short items in published articles between the two groups.

#### Secondary outcomes

Secondary outcomes will include the following:

Mean proportion of adequately reported C-short items in published articles considering each item separately.Difference in mean proportion of adequately reported C-short items in published articles considering each sub-item (see ‘Assessment of outcomes’) as a separate item.Time from assigning an editor to the first decision (as communicated to the author after the first round of peer review).Proportion of manuscripts rejected after the first round of peer review.Proportion of manuscripts that will be published in the journal under study.

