#### Inclusion criteria for manuscripts

All new manuscript submissions reporting the primary results of RCTs, which the journal editor has decided to send out for external peer review. Since the 10 chosen CONSORT checklist items (C-short) are applicable to different study designs, we will include all manuscripts reporting the primary results of RCTs regardless of study design (eg, parallel group trial, cluster trial, superiority trial, non-inferiority/equivalence trials).

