#### Exclusion criteria for manuscripts

Manuscripts clearly presenting secondary trial results, additional time points, economic analyses or any other analyses.Manuscripts which are clearly labelled as a pilot or feasibility study or animal studies.Manuscripts not sent for peer review.

Details of journal manuscript submission and peer review processes, including consent and potential confidentiality issues, will be discussed in detail with each journal by teleconference and/or face to face prior to the journal agreeing to take part to ensure that randomisation of manuscripts is feasible.

In participating journals, the external researcher (BS) will check at least twice a week (by screening automated submission lists) all research manuscripts that are sent out for external peer review. As soon as the first invited peer reviewer accepts the invitation to review, the manuscript will be randomised to the intervention or control arm (see ‘Randomisation’ for more details). It is possible that this process might be slightly different among various included journals (eg, that team members of a journal might be involved in the screening if limited or no access to the journal’s editorial system is granted).

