#### Intervention group: C-short plus usual practice

After accepting to review a manuscript, peer reviewers will receive the automated, journal specific standard email with general information (identical to control group). In addition, peer reviewers will receive an additional email from the editorial office that includes a short version of the CONSORT checklist (C-short) together with a brief explanation of the items either as a table within the email or as an attachment based on the preferences and possibilities of the journal (table 1, online supplementary appendix 1). Peer reviewers will be asked to check whether the items in the C-short checklist are addressed in the manuscript and to request authors to include these items if they are not adequately reported. This second email (see online supplementary appendix 1), containing the C-short checklist together with a brief explanation, is not generated automatically within the existing journal editorial systems (eg, ScholarOne or Editorial Manager); it will be sent manually by a researcher (BS) from the journal’s editorial system or by a member of the journal’s staff. In both cases the email will appear to have come from the editorial office (not the researcher).

10.1136/bmjopen-2019-035114.supp1Supplementary data

**Table 1 T1:** The 10 most important and poorly reported consort items as defined by a group of experts on the CONSORT statement.^30^for better understanding key features were summarised within a short explanation (extracted from the CONSORT explanation and elaboration paper^11^ as well as from the COBWEB tool)^33^

Item	Section	CONSORT item	Short explanation
1	Outcomes (6a)	Completely defined pre-specified primary outcome measure, including how and when it was assessed	Is it clear (i) what the primary outcome is (usually the one used in the sample size calculation), (ii) how it was measured (if relevant; eg, which score used), (iii) at what time point and (iv) what the analysis metric was (eg, change from baseline, final value)?
2	Sample size (7a)	How sample size was determined	Is there a clear description of how the sample size was determined, including (i) the estimated outcomes in each group, (ii) the α (type I) error level, (iii) the statistical power (or the β (type II) error level) and (iv) for continuous outcomes, the SD of the measurements?

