#### Assessment of outcomes

The outcomes will be assessed independently by two (blinded or at least partially blinded; see ‘blinding’) outcome assessors with expertise in the design and reporting of clinical trials. Any disagreement will be resolved by consensus or if necessary by consulting a third assessor. To ensure consistency between reviewers, we will first pilot the data extraction form; any disparities in the interpretation will be discussed and the data extraction form will be modified accordingly.

Adequate reporting of items will be assessed in duplicate from published full-text publications following the same instructions as provided by the CONSORT C-short checklist.^11^ The following checklist items have, due to their complexity, sub-items which will be extracted separately. The sub-items are highlighted in the short explanation of the intervention (see table 1 and online supplementary appendix 1):

Outcomes (item 6a): (i) define primary outcome, (ii) how it was measured, (iii) at what time point and (iv) the analysis metric (eg, change from baseline, final value).Sample size (item 7a): (i) the estimated outcomes in each group, (ii) the α (type I) error level, (iii) the statistical power (or the β (type II) error level), (iv) for continuous outcomes, the SD of the measurements.Blinding (item 11a): Is the blinding status clear for the following persons: (i) healthcare provider, (ii) patients and (iii) outcome assessors.Funding (item 25): (i) the funding source, and (ii) the role of funder in the design, conduct, analysis and reporting.

All items will be judged as either ‘yes’ meaning adequately reported, ‘no’ meaning not adequately reported or not reported at all, or ‘NA’ meaning that this sub-item is not applicable for this RCT. Items with different sub-items will only be judged as adequately reported if all relevant sub-items were adequately reported.

The outcomes ‘time from assigning an editor to the first decision’, ‘proportion of manuscripts rejected after the first round of peer-review’ and ‘proportion of manuscripts that will be published in the journal under study’ will be extracted directly from the journal’s editorial system or provided by the journal.

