### Participant timeline

The overview of the study schedule, including enrolment, intervention and assessments, is presented in table 2.

**Table 2 T2:** Study schedule

	Enrolment	Allocation and intervention	Intervention	Post-intervention	
Time point	Studies which are sent out for peer review	After first peer reviewer accepts invitation	Whenever an additional peer reviewer accepts invitation	First decision by journal	Published manuscripts
Eligibility screen	X				
Allocation		X			
Intervention:					
C-short + usual care		X	X		
Usual care		X	X		
Assessment of trial characteristics:					
Funding source					X
Study centres (single centre or multicentre)					X
Sample size					X
Study design (eg, parallel arm, crossover)					X
Hypothesis (eg, superiority, non-inferiority)					X
Medical field					X
Intervention tested					X
Number of trial arms					X
Number of peer reviewers					X
Journal which published the manuscript					X
Number of journals requesting CONSORT adherence (submission of checklist mandatory)					X
Assessment of outcomes:					
Time from assigning an academic editor until the first decision				X	
Proportion of manuscripts directly rejected after the first round of peer review				X	
Proportion of manuscripts that will be published in the journal under study					X
Adherence to CONSORT items and sub-items					X

CONSORT, CONsolidated Standards of Reporting Trials.

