### Data management and confidentiality

Outcomes from publications will be assessed and extracted in duplicate. Since this information is not confidential, we will use freely available online forms (eg, Google forms) for data extraction from published RCTs. Data entered will be validated for completeness.

Data from the journal’s editorial system (eg, title of manuscript, first author, randomisation ID, journal, date when manuscript was assigned to an editor, date when the final decision was made, final editorial decision, number of peer reviewers who reviewed the manuscript, the peer review reports (if available)) will be extracted (by BS or a member of the journal’s staff), anonymised and entered in password protected files which are saved on a server from the University of Oxford. Data will be managed and curated according to University of Oxford regulations, which includes regular back-up (on a daily basis) of the virtual drives where the data are stored. No auditing or data monitoring is planned (as outcomes are directly extracted from journal’s editorial system or in duplicate from published RCTs).

The raw data extracted from the included published manuscripts can be made openly accessible in an anonymised way (ie, giving the included RCT a number instead of identifying them). Derived/aggregated data, including anonymised information generated from the journal’s editorial system, will be stored and made available to the research community when the project ends (see also ‘Publication policy and access to data’). Where appropriate, the researcher who has access to the journal’s editorial system (BS) and anyone else who will see the identifiable data will sign a confidentially agreement with the participating journals, confirming that they will not share identifiable data with any other party. Publishers such as the British Medical Journal (BMJ) state in their Company Privacy Statement that reviews and manuscripts may be used for quality improvement purposes and that is the nature of this research. Furthermore, peer reviewers for all BMJ journals receive the following statement in their invitation letter ‘We are constantly trying to find ways of improving the peer review system and have an ongoing programme of research. If you do not wish your review entered into a study please let us know by emailing […] as soon as possible.’

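### Time to first decision is counted from editor assignment, so a pre-randomisation interval the intervention cannot affect adds avoidable variance to this secondary outcome

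*Protocol article*

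**What the plan says.** - **The clock.** The Secondary outcomes section of the protocol article lists "Time from assigning an editor to the first decision (as communicated to the author after the first round of peer review". The study schedule (Table 2, under Participant timeline) has the same start and stop: "Time from assigning an academic editor until the first decision". The Assessment of outcomes section says that this outcome "will be extracted directly from the journal’s editorial system or provided by the journal".
- **Enrolment.** Eligible manuscripts are those "which the journal editor has decided to send out for external peer review", so an editor has already acted before a manuscript can enter the trial.
- **Randomisation.** "As soon as the first invited peer reviewer accepts the invitation to review, the manuscript will be randomised to the intervention or control arm". The section on randomisation and blinding says the same.
- **Intervention.** Both arms first get the journal's usual message: "After accepting to review a manuscript, peer reviewers will receive the automated, journal specific standard email with general information (identical to control group". The checklist email is sent in addition to it, so it too comes after acceptance.
- **Analysis.** Secondary outcomes are compared by mean differences with 95% CIs, or by a rank test if a continuous outcome is not normal. No covariate is described. Time to first decision is calculated in published manuscripts and additionally in all randomised manuscripts (Populations of analysis).
- **Dates to be extracted.** Among its examples of data taken from editorial systems, the Data management and confidentiality section names "date when manuscript was assigned to an editor, date when the final decision was made, final editorial decision". It does not name a first-decision date.

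**The concern.** The outcome starts at an event that precedes allocation. The time from editor assignment to the first reviewer's acceptance depends on the editor's workload and on how hard it is to find a reviewer. It is over before either arm exists. Counting it adds manuscript-to-manuscript variation that carries no information about the intervention.

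This is the only listed outcome that shows whether the extra reviewer task slows the journal's process. The article argues that the intervention could be adopted without large additional resources, so journals will probably read this comparison for reassurance. An unnecessarily wide interval makes a real delay easier to miss and an absence of delay harder to support.

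A smaller matter is that the listed end date is that of the final decision. Time to a final decision can include the authors' revision time and later review rounds, which is not what the outcome defines.

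**Working it through.** **Order of events, from the sections cited above**

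1. Editor assigned: the clock starts.
2. Editor decides to send the manuscript out, and reviewers are invited.
3. First reviewer accepts, which triggers randomisation.
4. Checklist email sent (intervention arm only).
5. First decision: the clock stops.

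Write T = A + B, where A is the time from editor assignment to randomisation and B the time from randomisation to first decision. Only B can respond to allocation.

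**Expected difference.** Among all randomised manuscripts, A has the same distribution in both arms in expectation. The expected difference in mean T therefore equals the expected difference in mean B. The choice of clock does not change what is estimated.

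**Variance.** Let r = Var(A)/Var(B). If A and B are uncorrelated, Var(T) = Var(B) × (1 + r), and the standard error of the mean difference is multiplied by sqrt(1 + r). With correlation ρ the variance factor is 1 + r + 2ρ·sqrt(r). Positive correlation makes the loss larger. The loss vanishes only if ρ is as negative as −sqrt(r)/2.

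**Inputs.** The article gives no SD, effect size or power for this outcome, so there is no stated figure to reproduce. The range of r below is an assumption. The 83 per arm is borrowed from the primary outcome only as a scale. That figure does reproduce: a difference of 0.11 with SD 0.25, two-sided 5% and 80% power needs 82.05 per arm by the t-test, rounded up to 83, with 80.5% power at 83.

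**Illustration.** Take an effect on B that would have 80% power with 83 per arm if the clock started at randomisation. Under the present clock, power = Φ[(1.960 + 0.842)/sqrt(1 + r) − 1.960]. The number per arm that restores 80% is 83 × (1 + r), rounded up.

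| r (assumed) | SE factor sqrt(1+r) | Power, present clock | Per arm to restore 80% |
|---|---|---|---|
| 0.1 | 1.05 | 76% | 92 |
| 0.25 | 1.12 | 71% | 104 |
| 0.5 | 1.22 | 63% | 125 |
| 1 | 1.41 | 51% | 166 |
| 2 | 1.73 | 37% | 249 |

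Example at r = 1: 2.802/1.414 = 1.981; 1.981 − 1.960 = 0.021; Φ(0.021) = 0.51.

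In days, if B had an SD of 25 and A an independent SD of 10, r = 100/625 = 0.16 and the standard error rises by 8%. If A also had an SD of 25, r = 1 and it rises by 41%. These SDs are assumed too.

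**Adjustment as the alternative.** Because T = A + B, a linear model with A as a covariate gives the same treatment estimate whether T or B is the response. Either route removes the variance that A contributes.

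**Extraction list.** The outcome definition, Table 2 and the Assessment of outcomes section all refer to the first decision. The data-management list names the date of the final one. That list is introduced as a set of examples and does not say that these dates define the time outcome.

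**The case against.** **No bias, and a coherent measure.** Allocation comes after the interval in question, so the comparison is fair. Total time from editor to decision is a figure journals can use, which suits a pragmatic trial. This stands. A reader might infer from the early start that the comparison is biased, but the documents do not support that. The cost is precision only. Strictly, balance is guaranteed for all randomised manuscripts. Publication is determined after allocation, so the published subset raises a separate question that arises under either clock.

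**The size is not known.** No SD is given for either segment. If the pre-randomisation interval varies little, the loss is negligible. The calculation also describes a comparison of means, not the rank test that may be used. All of this stands, and the table shows what could happen, not what will.

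**Adjustment may be in the analysis plan.** Covariates are commonly left to that document, which is not shown. This is fair as far as adjustment goes. The start of the clock, however, is fixed in the article itself, in three places.

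**The first decision will be collected.** A reader might infer from the data-management list that the first-decision date will not be recorded and that the outcome would become time to final decision. The text does not support this. The list is illustrative, and the Assessment of outcomes section says the time to first decision will be taken from the editorial system or supplied by the journal. The final decision is also relevant to another secondary outcome, the proportion published. What remains is an incomplete list.

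**Analysis of all randomised manuscripts.** It would be wrong to say this is missing. It is already planned as an addition for this very outcome.

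**The randomisation time is not exactly the acceptance time.** Screening is at least twice a week and randomisation is entered by hand, so the logged time may lag first acceptance by a few days. This stands as a small drawback of the remedy.

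**Conclusion.** The point holds as a matter of efficiency. The outcome includes an interval that ends before allocation, and the unadjusted comparison described leaves its variance in the standard error. The mean difference stays unbiased in the analysis of all randomised manuscripts. The loss is a factor of sqrt(1 + r) on the standard error if the two segments are uncorrelated: 1.05 at r = 0.1 and 1.41 at r = 1. Where r lies cannot be determined from the document, and the loss could be small.

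The extraction list is a minor inconsistency to tidy up, not evidence that the outcome will be mismeasured. The primary outcome and its sample size are not touched. The change is worth making because it is cheap and keeps the same expected difference, normally with a narrower interval.

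**What to change.** 1. Define the outcome as time from randomisation to first decision. Alternatively, keep the editor-assignment clock and adjust for the interval from assignment to randomisation as a baseline covariate. State the choice before the data are examined.
2. Report total editor-to-decision time by arm descriptively, so that journals keep the familiar figure.
3. In the Data management and confidentiality section, add the date and type of the first decision to the examples. The type is needed for the outcome on rejection after the first review round. Add the randomisation date as well.

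The cost is wording, plus linking one further date per manuscript from the randomisation system to the editorial data. If first acceptance is preferred as the start, because the logged randomisation may come a few days later, the acceptance date would have to be extracted as well. No change to sample size, recruitment or the primary analysis follows.

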#### Additional outcomes

Exploratory analysis of available peer reviewer comments (ie, any references to CONSORT).

For journals where peer reviewers’ comments are subsequently published alongside the published article, we will examine the peer reviewers’ comments for any reference to CONSORT and trial reporting. We will contact those journals which do not make peer reviewers’ comments publicly available, to see if reviews could be provided for such analyses under the condition that only anonymised data will be published.

#### Assessment of outcomes

The outcomes will be assessed independently by two (blinded or at least partially blinded; see ‘blinding’) outcome assessors with expertise in the design and reporting of clinical trials. Any disagreement will be resolved by consensus or if necessary by consulting a third assessor. To ensure consistency between reviewers, we will first pilot the data extraction form; any disparities in the interpretation will be discussed and the data extraction form will be modified accordingly.

Adequate reporting of items will be assessed in duplicate from published full-text publications following the same instructions as provided by the CONSORT C-short checklist.^11^ The following checklist items have, due to their complexity, sub-items which will be extracted separately. The sub-items are highlighted in the short explanation of the intervention (see table 1 and online supplementary appendix 1):

Outcomes (item 6a): (i) define primary outcome, (ii) how it was measured, (iii) at what time point and (iv) the analysis metric (eg, change from baseline, final value).Sample size (item 7a): (i) the estimated outcomes in each group, (ii) the α (type I) error level, (iii) the statistical power (or the β (type II) error level), (iv) for continuous outcomes, the SD of the measurements.Blinding (item 11a): Is the blinding status clear for the following persons: (i) healthcare provider, (ii) patients and (iii) outcome assessors.Funding (item 25): (i) the funding source, and (ii) the role of funder in the design, conduct, analysis and reporting.

All items will be judged as either ‘yes’ meaning adequately reported, ‘no’ meaning not adequately reported or not reported at all, or ‘NA’ meaning that this sub-item is not applicable for this RCT. Items with different sub-items will only be judged as adequately reported if all relevant sub-items were adequately reported.

The outcomes ‘time from assigning an editor to the first decision’, ‘proportion of manuscripts rejected after the first round of peer-review’ and ‘proportion of manuscripts that will be published in the journal under study’ will be extracted directly from the journal’s editorial system or provided by the journal.

